#### fMRI statistical analysis

All functional volumes will be preprocessed and analyzed using SPM12 software (http://www.fil.ion.ucl.ac.uk/spm), implementing a standard pipeline which includes spatial realignment, slice-timing correction, anatomo-functional coregistration, normalization to the Montreal Neurological Institute (MNI) template and smoothing. At group level, significant brain activations will be assessed using the General Linear Model (GLM). Parametric maps (*t* contrast) of the activation will be calculated in the whole brain for each experimental and control condition. Subsequently, to assess possible differences between subjects, a ROI (Regions of Interest) analysis will be performed in the main MNS areas, extracting the BOLD signal associated with each condition. Student’s t-test will be used to evaluate the significance of BOLD signal differences between conditions. All parametric statistical maps will be corrected for multiple comparisons by applying the Family Wise Error (FWE) method, with a significance level set at *p* < 0.001. In addition to the univariate statistical analysis, advanced analyses including Psychophysiological Interaction and Dynamic Causal Modeling will be performed in order to measure effective functional connectivity changes between MNS areas, following the application of the rehabilitation treatment.

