Several studies support the application of VR methods in the rehabilitation of the hemiplegic upper limb in stroke patients [26]. The largest study conducted to date involved 376 patients and demonstrated a positive effect of VR-based rehabilitation [27]. Moreover, recent literature reviews [28] have provided evidence for improvement in upper limb motor function and daily life activity after VR-based training compared with standard interventions. However, clinical evidence based on rigorous RCTs on the effect of the combined use of observation of actions followed by their immediate imitation in a VR environment (AO + VR therapy) is lacking, especially in the case of rehabilitation applied during the chronic phase after a stroke.

The main hypothesis of the study is that, for the recovery of motor function of hemiplegic stroke patients in the chronic phase, a combined rehabilitation treatment (AO + VR therapy) is more effective than a control treatment (control observation – CO) based on the observation of videos without motor content (e.g., environmental natural scenes), followed by the execution of actions in VR (CO + VR control therapy).

In sum, the planned trial will examine the following hypotheses:

AO + VR is an effective tool for promoting upper limb control in paretic stroke patients, and its effects are greater than CO + VR control treatment.Motor performance, cognitive level, and structural brain damage assessed before treatment are correlated to the degree of improvement resulting from the AO + VR intervention.The AO + VR intervention results in greater plastic functional changes of the MNS activity compared with the effects of the CO + VR control treatment.

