#### Functional MRI study

A subgroup of participants (approximately 20 individuals equally distributed in the two groups, i.e., 10 for experimental and 10 for control group) will be involved in a functional MRI (fMRI) study, to assess plastic changes in the MNS activity following the application of the rehabilitation treatments. fMRI will be performed in two sessions, one before (T0) and one after the end of the treatment (T1) within 72 h. Before starting each functional imaging session, participants will undergo a training session lasting 15 min, in order to allow them to familiarize with the MR system and the experimental procedure. After, patients will be invited to participate in the real fMRI session (divided into 4 short runs lasting approximately 7 min each).

The patient will be instructed to perform two experimental tasks: a) *action observation* (functional runs 1–2); b) *motor task* (functional runs 3–4).

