#### Action observation

During the first two functional runs, visual stimuli will be presented in binocular vision by means of Liquid Cristal Display (LCD) goggles (VisuaStim-SVGA-Resonance Technology, USA). Participants will observe short video-clips (lasting 4 s each), showing unimanual or bimanual actions performed by an actor, from a subjective perspective. The observed actions will consist in grasping and using different tools (e.g., hammering, using a screwdriver, opening a jar etc.), or as control condition, observation of the static initial frame of each clip. The objects will be of different colors in order to increase the visual variability of the stimuli. The visual characteristics of each video will be balanced between the experimental conditions to control the effects of brightness, contrast, sharpness and the amount of visual information. A total of 72 video clips will be created (9 objects × 4 colors × 2 conditions).

Each experimental and control condition will be presented 72 times during the experiment, 36 times for each session. The videos will be presented in independent blocks (*N* = 12) for each condition and each block will contain 6 videos, interspersed with an inter-stimulus period of 800 ms. The duration of each block will be 28 s. A number of 12 blocks will be acquired in each observation run, 6 per condition, followed by a variable *rest* period, lasting 16-20 s. During the *rest* period, in the absence of experimental stimuli, the patients will have to fixate a white cross on a black background.

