Concerning the role of MNS plastic reorganization in improving motor learning, lesion localization could represent a limiting factor when the lesion affects the cortical areas associated with MNS activity. Nonetheless, a large network of cortical and subcortical areas may provide multiple compensation mechanisms, facilitating motor re-learning in hemiplegic chronic patients. Thus, imaging studies are crucial to explore the potential of the MNS for rehabilitation and to determine which patients may benefit from specific types of AOT treatments. The fMRI assessment included in this protocol specifically aims to investigate the possible functional changes in the MNS activity of patients treated with AO + VR intervention compared to those treated with the control intervention. In particular, this investigation may allow a direct comparison of the patient’s brain activation during the observation and execution of goal-directed actions, enabling the study, for example, of the lateralization of neural activation and the extension of the activated clusters within the MSN. Also, the degree and lateralization of activation in the ipsilesional/contralesional hemisphere may correlate with improvements in arm/hand motor function parameters assessed through the primary and secondary motor outcome measures. This analysis will make it possible to identify the clinical features of stroke patients who would benefit most from AO + VR treatment, thus strengthening the evidence of its effectiveness in specific patients.

The integrated approach described in the present protocol requires a multi-professional team, to plan well-designed randomized controlled trials with the possibility of correlating measures of functional outcomes, neuropsychological assessment, and biological parameters obtained using brain imaging techniques.

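### The only test named for the fMRI regions of interest compares scanner conditions, so it does not test hypothesis 3, that MNS activity changes more under AO + VR than under CO + VR

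*Protocol article*

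**What the plan says.** The third hypothesis in the Background is that the AO + VR "intervention results in greater plastic functional changes of the MNS activity compared with the effects of the CO + VR control treatment". The Discussion gives the same aim for the imaging part: to study "functional changes in the MNS activity of patients treated with AO + VR intervention compared to those treated with the control intervention". Under Functional MRI study, patients are scanned at T0 and at T1, and the subgroup is "approximately 20 individuals equally distributed in the two groups, i.e., 10 for experimental and 10 for control group".

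The section fMRI statistical analysis plans whole-brain t-contrast maps for each experimental and control condition. It then adds an ROI step: "to assess possible differences between subjects, a ROI (Regions of Interest) analysis will be performed in the main MNS areas". The BOLD signal is extracted per condition, and the one test named is Student's "t-test will be used to evaluate the significance of BOLD signal differences between conditions". Connectivity analyses follow; they address change after treatment and mention no comparison of arms.

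The two task sections define *condition*. In the observation task, patients see action clips "or as control condition, observation of the static initial frame of each clip". In the motor task, the comparison is tool manipulation against reaching without manipulation.

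**The concern.** Hypothesis 3 is a between-arm difference in T0-to-T1 change. It needs treatment arm and visit in the model, and the named ROI test has neither. A t-test of action against static frame asks whether the task engages the MNS. That can be true at both visits and in both arms with no treatment effect at all.

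One of the trial's three stated hypotheses would therefore have no test directed at it. A significant condition difference could be reported under the heading of plastic change although it carries no information on whether AO + VR changed anything more than CO + VR did.

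**Working it through.** **1. The two quantities.** Let C(arm, visit) be the mean condition contrast (action minus static, or manipulation minus reaching) in one ROI.

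- Hypothesis 3: [C(AO, T1) − C(AO, T0)] − [C(CO, T1) − C(CO, T0)] > 0.
- Stated test: is C different from 0?

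If all four means equal 1, the stated test has a real effect to find, while the first quantity is (1 − 1) − (1 − 1) = 0. The answer to the one does not determine the answer to the other.

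**2. Simulation.** Assumed inputs, none of them from the article: contrast SD 1 at each visit, T0–T1 correlation 0.5, normal data, 20,000 runs. The 10 per arm is the article's figure. The condition test is a one-sample t-test on each patient's two-visit mean contrast, all 20 patients pooled. The arm-by-time test is an independent-samples t-test on T1 − T0. Both are two-sided at 0.05.

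| Condition effect | Extra change in AO + VR | Condition test significant | Arm-by-time test significant |
|---|---|---|---|
| 1 SD | 0 | 99.8% | 5.0% |
| 1 SD | 1 SD | about 100% | 56% |
| 0 | 0 | 5.3% | 4.9% |

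Plausibility check of the first row: the two-visit mean has variance (1 + 0.5)/2 = 0.75 and SD 0.866. The noncentrality is therefore (1/0.866) × √20 = 5.16, for which power near 100% is expected. With a condition effect of this size, the test is almost certain to be significant whether hypothesis 3 is true or false.

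**3. The article's own fMRI sample size.** The section Sample size gives at least 9 per group for 80% power to obtain a change in BOLD signal at p < 0.05 with Bonferroni correction. This cannot be reproduced, because the effect size, variance and number of corrected tests are not given. What can be computed is the standardized effect detectable with 80% power (two-sided, noncentral t):

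| n per arm | Within-subject contrast, alpha 0.05 | Between-arm difference in change, alpha 0.05 | Between-arm, alpha 0.025 (two ROIs assumed) |
|---|---|---|---|
| 9 | 1.07 | 1.41 | 1.58 |
| 10 | 1.00 | 1.33 | 1.48 |

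The normal approximation for 10 per arm, (1.96 + 0.84) × √(2/10) = 1.25, is a little below the exact 1.33, as expected in so small a sample.

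At the effects that a within-subject contrast could just detect (1.07 and 1.00), the between-arm test has about 57% and 56% power. It would need about 15 and 17 per arm to reach 80%.

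**4. ANCOVA against change score.** With equal variances and T0–T1 correlation r, the SD of change is σ√(2(1 − r)) and the ANCOVA residual SD is σ√(1 − r²). Their ratio is √((1 + r)/2): 0.806, 0.866 and 0.922 for r = 0.3, 0.5 and 0.7. Ignoring the one degree of freedom spent on the covariate, the detectable difference of 1.325 SD of change (1.33 rounded) falls to about 1.07, 1.15 and 1.22. The two models differ, and ANCOVA is somewhat more precise, but the detectable effect stays large.

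**The case against.** The strongest defence is that a comparison of arms was clearly intended. The ROI step is introduced as looking at differences between subjects, a group-level general linear model is planned, the sample-size section speaks of BOLD change after treatment, and the Discussion states the between-arm aim. Testing task contrasts is an ordinary first step and does not exclude a later group-by-session contrast. A journal article may leave second-level modelling to a fuller document.

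The intention can be granted. But this is more than missing detail: the article names a test, and that test has a different target. The section just before it states a group-by-time design for the clinical outcomes, so the difference is visible within the article itself.

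The defence is right about importance. The imaging subgroup is about 20 of 94 patients, fMRI is neither the primary nor a listed secondary outcome, and a single-case reading is planned as well.

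A reader might infer two stronger things that the documents do not support:

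- **Imaging patients are chosen after allocation is known.** Nothing says so. The MRI criteria stand with the eligibility criteria, and 1:1 allocation in permuted blocks would by itself give roughly equal numbers.
- **Significance will be judged separately in each arm and then contrasted.** No such procedure is stated, so an error rate worked out for it would not describe this plan.

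**Conclusion.** The point holds. As written, the only named ROI test does not answer hypothesis 3, and neither the whole-brain maps nor the connectivity analyses are given an arm comparison that would. This conclusion rests on the article's own use of *condition* and on step 1 of the check; it does not depend on the simulation settings.

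The correctly targeted test is much less sensitive than the sample-size statement suggests. With 10 per arm it has 80% power for about 1.33 SD of change at two-sided 0.05, and for about 1.48 if two ROIs are Bonferroni-corrected (the number of ROIs is an assumption). These figures are for the change-score test.

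This is a correction worth making to a subgroup hypothesis. It leaves the Box and Block Test analysis and its conclusion untouched, so it should not be read as a flaw in the trial's main efficacy result.

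**What to change.** In fMRI statistical analysis:

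1. Name the MNS ROIs in advance. For each, compute the condition contrast (action minus static; manipulation minus reaching) at T0 and at T1.
2. Compare arms on the T1 contrast by ANCOVA with the T0 contrast as covariate, and report the adjusted difference with its confidence interval. State this as the one chosen model. The arm-by-time test on change scores is an alternative, not an equivalent: it fixes the baseline slope at 1, whereas ANCOVA estimates it.
3. Apply Holm or Bonferroni correction across the ROIs, and across the two tasks if both are to carry the hypothesis.
4. Use the group-by-session contrast for the whole-brain maps and for the connectivity measures.
5. Keep the between-condition t-test, described as a check that the tasks activate the MNS.

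In Sample size, describe the minimum of 9 per group as sized for a change in BOLD signal and not for the between-arm difference, and give the detectable difference for the latter.

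The cost is wording: no extra scans or visits. The statistical price is the low power shown above, so a null between-arm result will be weak evidence of no difference. Recruitment had not begun when the article was submitted; the change should be fixed before imaging data are examined.

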#### Study Status

At the time of the submission of this study protocol, recruitment has not yet started.

#### Dissemination policy

The results of the study will be released to the participating patients and to the general medical and neuroscientific community. Every attempt will be made to reduce the minimum interval between the completion of data collection and the release of the study results. We expect to take about 3 to 4 months to draft the results paper for an appropriate peer-reviewed journal.

## Discussion

The present study protocol describes the background and the design for a randomized controlled six-month follow-up trial (RCT) to evaluate the efficacy of AOT combined with VR techniques in improving upper limb activity in patients with stroke. The main hypothesis is that a VR-based therapeutic intervention associated with the systematic observation of actions performed by a model (AO + VR) could increase motor facilitation and, as a consequence, improve upper limb control and function.

The contribution of this study will be significant because the recovery of upper limb function in patients following a stroke represents a challenge for every rehabilitative team. In fact, the traditional rehabilitative approach has substantial and intrinsic limitations in modifying the clinical history of upper limb motor impairment and functional ability. The proposed research is innovative because it is based on a rigorous scientific design and follows CONSORT guidelines, as recommended by evidence-based medicine. Furthermore, it can produce viable targets for future studies that test the effectiveness of rehabilitative interventions for other motor deficits in neurological patients.

The set of AO + VR exercises created for the RCT are goal-oriented and tailored according to the degree of upper limb impairment. This type of personalized treatment allows the adaptation of the exercises to each patient’s upper limb clinical characteristics by proposing specific movements/actions suitable for the patient’s motor repertoire. A specific set of bimanual exercises comprising daily life actions was also included in the rehabilitation treatment, chosen on the basis of their ecological value. Another important feature of the study is that the combined use of action imitation and a VR environment could be useful in activating the motor system in pathological conditions in which intensive motor training is not feasible due to the severity of the impairment. These types of treatments are generally well accepted by patients because they offer an engaging environment and greater adaptability to the patient’s clinical features and progress, as well as the opportunity for patients to record their motor performance. Furthermore, VR exercises usually require minimal supervision by expert therapists, thereby facilitating individualized home-based tele-rehabilitation.

Concerning the role of MNS plastic reorganization in improving motor learning, lesion localization could represent a limiting factor when the lesion affects the cortical areas associated with MNS activity. Nonetheless, a large network of cortical and subcortical areas may provide multiple compensation mechanisms, facilitating motor re-learning in hemiplegic chronic patients. Thus, imaging studies are crucial to explore the potential of the MNS for rehabilitation and to determine which patients may benefit from specific types of AOT treatments. The fMRI assessment included in this protocol specifically aims to investigate the possible functional changes in the MNS activity of patients treated with AO + VR intervention compared to those treated with the control intervention. In particular, this investigation may allow a direct comparison of the patient’s brain activation during the observation and execution of goal-directed actions, enabling the study, for example, of the lateralization of neural activation and the extension of the activated clusters within the MSN. Also, the degree and lateralization of activation in the ipsilesional/contralesional hemisphere may correlate with improvements in arm/hand motor function parameters assessed through the primary and secondary motor outcome measures. This analysis will make it possible to identify the clinical features of stroke patients who would benefit most from AO + VR treatment, thus strengthening the evidence of its effectiveness in specific patients.

The integrated approach described in the present protocol requires a multi-professional team, to plan well-designed randomized controlled trials with the possibility of correlating measures of functional outcomes, neuropsychological assessment, and biological parameters obtained using brain imaging techniques.

## Data Availability

The datasets used and/or analyzed during the current study will be available from the corresponding author on reasonable request.

## Abbreviations

AO: Action observation
AOT: Action observation therapy
AO + VR: Experimental treatment based on action observation and virtual reality
BBT: Box and Block Test
BOLD: Blood oxygenation level dependent
CO: Control observation
CO + VR: Control treatment based on observation of control videos and virtual reality
CRF: Case report form
DICOM: Digital Imaging and Communications in Medicine
DTI: Diffusion Tensor Imaging
EPI: Echo-planar imaging
FOV: Field of view
fMRI: Functional magnetic resonance imaging
FEW: Family wise error
GLM: General linear model
IFG: Inferior frontal gyrus
IPL: Inferior parietal lobule
LCD: Liquid cristal display
LMM: Linear mixed model
MAS: Modified Ashworth scale
mBI: Modified Barthel index
MI: Motricity index
MMSE: Mini mental state examination
MNI: Montreal Neurological Institute
MNS: Mirror neuron system
MRC: Medical Research Council
MRI: Magnetic resonance imaging
OT: Occupational therapist
PMv: Ventral premotor cortex
PACS: Picture Archive Computed System
PT: Physiotherapist
rmANOVA: Repeated measures analysis of variance
ROI: Region of interest
RS: Rankin scale
TE: Echo time
TR: Repetition time
UCP: Unilateral cerebral palsy
VR: Virtual reality
VRRS: Virtual Reality Rehabilitation System
